### 3.4 Methods

*Pulse wave measurements*

Measurement of pulse wave is done by using applanation tonometry, which is non-invasive. Applanation tonometry provides information on the peripheral pulse wave morphology. The shape of the pulse wave is the sum of the forward going wave and the reflected wave. The reflected wave arises as a reflection of the incident wave form the periphery. In healthy individuals without atherosclerotic plaques or arteriosclerotic vessels the reflected wave returns in late systole or early diastole of the cardiac cycle. In people with arteriosclerosis the reflected wave returns earlier in systole, thereby compromising the filling of the coronary arteries and increasing the load on the ventricles leading to increased central blood pressure, left ventricular hypertrophy and increased risk of stroke and myocardial infarction. By using mathematical calculations in the generalized transfer function, built in in the SphygmoCor® device, information can be gained on the central blood pressure (aorta ascendens) from measurements performed on peripheral arteries (a. radialis). Validation of the pulse wave transfer function has been done invasively and it is now generally accepted as the gold standard for assessing arterial stiffness (41). Several studies have shown good reproducibility with acceptable inter- and intraobserver variation (42-45).

Pulse wave measurements are performed by the same, trained observer in the morning under standardized conditions. Before performing the actual measurements, marks are made on the skin of the patient over the part of the a. radialis, a. carotis, and a. femoralis where the pulse is most prominent. The suprasternal notch (SN) is used as reference point and is also marked. A tape measure is used to measure the distances between the SN and a. radialis, carotid artery and a. femoralis, respectively. Patients are then requested to rest in the supine position, in a quiet room of constant temperature for 10 minutes. The measurements are all undertaken on the right side. Patients have to be in the fasting state and have to refrain from smoking 8 hours before examination. Diabetics are allowed a light meal and all participants are allowed a glass of water. All medications including study medication are to be taken after examination. Quality of the measurements is evaluated partly by a visually acceptable curve of the peripheral pulse wave and partly by a maximum difference between 2 successive measurements of ≤7% and an average height of the wave of > 80 mV(42). Pulse wave measurements are done in two sets. The first is the pulse wave (PW) and after this the PWV. The AIx is derived from the PW. It is calculated as the percentage of augmentation (AG) of the pulse pressure (PP). On the recordings of the peripheral waves the PP, the first peak of the pulse wave (P1) and the second peak (P2) are marked. The augmentation is the difference between P1 and P2. And the AIx is this difference taken out of the PP. These calculations are all performed automatically by the SphygmoCor software. An acceptable Quality Index (QI) is > 80%. QI is calculated by the software from the other stated quality indicators (pulse height, max. 7 % difference between two measurements).

*Ambulatory blood pressure measurements*

AMBPs are automatically measured blood pressures during ordinary daily activities for a time period of approximately 24 hours. AMBP has been found reproducible in population studies (25-30), hypertensive populations (46) and diabetics (47). The reproducibility of AASI has been proven less reliable in an essentially hypertensive population (48) . The brachial BP is measured in the office using the ABPM equipment on the non-dominant arm. After manual measurements the apparatus will automatically measure the BP every 15 minutes in daytime, which is defined from 7 am until 11 pm. Hereafter the measurements will be performed every 30 minutes from 11 pm till 7 am (49). All patients receive a diary in which they are to make notes of physical activity, meals and rest as well as bedtime and rising time in the morning. For calculation of AASI a minimum of 21 readings of BP is required. These must be spread out over the whole period with at least 7 successful readings during night time. AASI is calculated in the following manner: (1-(the slope of diastolic BP/slope of systolic BP)). It follows that the stiffer the arterial tree, the more the regression line will go towards 0 and AASI thus towards 1. Previous studies have provided references for AASI in the background population. AASI for normotensive individuals is 0.57. In younger individuals AASI is 0.53 increasing to 0.72 in the elderly (30).

*Intervention – study medication*

The study medication is eplerenone, a selective aldosterone receptor antagonist. It is an approved drug, which in this study will be used on a non-appraised indication. The Summaries of Product Characteristics (SPC) in Danish will be used as reference document for evaluation of possible side effects and will be accessible at the site of investigation when the study is initiated.

Initial recommended dose is 25 mg once daily. The dose will be increased to 50 mg eplerenone in once daily dosing after 1 week. In this study eplerenone will be added to the study participants’ usual medication. The manufacturing company Pfizer Aps has been informed of the study.

*Control*

The control group will continue their usual medical therapy.

All dispensed study medication is registered in the participant’s CRF. At all visits compliance is noted and counts of tablets are made at the end of the study period. The study medication is provided by the hospital pharmacy in usual packages, with note of batch number and expiry date. Participants will be carefully instructed in the importance of compliance regarding study medication and participation as a whole.

Labels for study medication will contain the following information (in Danish):

*For use in clinical trial ALBLOCK-2*

*Patient no: ____ Visit no:___ No. tablets:______*

*Dose: 1 tablet daily. Should be taken in whole.*

*Unused medicine and empty packages to be returned to [name]*

*Sponsor-investgator: MD [name], Dept. Nephrology, Herlev Hospital [name]*

*Storage: At max 25°C out of reach of children.*

*In case of emergency please contact [name]*

*EudraCTno: 2009-012445-35*

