### 3.2 Design

The study is a prospective, randomized, controlled, parallel group, phase IV study.

| Week number | -4 | 1 | 2 | 4 | 8 | 12 | 16 | 20 | 24 |
| --- | --- | --- | --- | --- | --- | --- | --- | --- | --- |
| Visit number |  | 1a/1b | 2 | 3 | 4 | 5a/5b | 6 | 7 | 8a/8b |

A BP target of 120-130/80-90 is set and investigators will strive to keep this constant in patients throughout their enrolled period. Therefore a run-in period of 4 weeks has been planned. All patients are to continue on their normal medication including blockers of RAS, which most of these patients receive before enrolment. If anti-hypertensive treatment needs to be intensified, this is done by adding beta blocker, calcium antagonist or methyldopa. If BP is lower than target pressure medication will be withdrawn, primarily via reduction in calcium antagonism or beta blockade, while RAS-blockade in the initial form is aimed to be kept as it was.

If study participants fail to tolerate the full dose of eplerenone 50 mg once daily, dose will be reduced to 25 mg once daily. In case of the patients receiving potassium supplements at time of enrolment these will be withdrawn before start of intervention.

Participants are randomized after the run-in period and are given consecutive numbers of identification.

The study plan is identical for the two groups.

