3.5 Randomization

Randomization is done by blocks that are of unknown size to the investigators and sponsor by drawing of sealed, opaque envelopes provided by the GCP-unit of Copenhagen University.

At the time of randomization patients are given consecutive numbers of participation. Randomization will take place after the informed consent forms have been signed and the run-in period has been completed. Numbers will be noted in the participants’ CRF and in the patients’ medical file.

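### The hand-taped path length behind PWV, the primary endpoint, can be measured with the arm known at baseline and follow-up, and no rule prevents it

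*Protocol*

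**What the plan says.** Section 3.2 gives the design: "The study is a prospective, randomized, controlled, parallel group, phase IV study". Section 3.4 says of the comparator: "The control group will continue their usual medical therapy". The drug is not disguised: "The study medication is provided by the hospital pharmacy in usual packages, with note of batch number and expiry date". The protocol nowhere describes masking of the patient, the observer or the person reading the recordings. Section 3.5 protects the assignment itself: "Randomization is done by blocks that are of unknown size to the investigators and sponsor by drawing of sealed, opaque envelopes".

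PWV is the primary endpoint (section 3.3). On who measures it, section 3.4 says: "Pulse wave measurements are performed by the same, trained observer in the morning under standardized conditions". The steps begin with marking ("Before performing the actual measurements, marks are made on the skin of the patient") and continue with taping ("A tape measure is used to measure the distances between the SN and a. radialis, carotid artery and a. femoralis, respectively"). Nothing says that the baseline distance is kept, that taping is duplicated, or that the observer is kept from the arm or from earlier values.

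Quality control is partly visual: "Quality of the measurements is evaluated partly by a visually acceptable curve of the peripheral pulse wave". It is also numeric: at most 7% difference between two successive measurements, mean wave height above 80 mV, and a software quality index above 80%.

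Pulse wave measurements are made at visits 1, 5a and 8a (section 3.11), plus a test at screening. In the visit table of section 3.13, the entry for visit 1a names randomization first and the pulse wave measurement second. At visits 5a and 8a the pulse wave measurement is listed first.

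**The concern.** PWV is a distance divided by a transit time. The device times the wave, but a person with a tape supplies the distance. In a trial where that person can know the arm, the distance is the input most open to expectation.

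The protocol leaves the route open at both ends. At visit 1a the listed order allows the baseline distance to be taped after the envelope is opened. At visits 5a and 8a no rule prevents a fresh taping by an observer who may know the arm. Concealed envelopes protect the assignment, not later assessment. The numeric limits concern the height, repeatability and quality of the recorded wave; a distance taped 1 cm long or short passes all of them.

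What is at stake is the between-arm difference in the primary endpoint. A systematic leaning by arm would enter it directly, and a larger sample would not remove it.

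**Working it through.** **Inputs from the protocol (Statistics section).** Target difference 1 m/s; SD 1.5; two-sided alpha 0.05; power 0.80; stated n = 36.3058, so 37 per group; 40 per group planned. The protocol does not say whether 1.5 is the SD of single values or of change.

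**Assumed inputs (not in the protocol).** PWV 8-12 m/s; path 45-60 cm; tape SD 0.5-2 cm; size of any between-arm bias.

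**1. The plan's own figure.** Solving the two-sample t test with the noncentral t gives n = 36.3057 per group, which rounds up to 37. Power is 80.8% at 37 and 83.8% at 40. The stated sample size reproduces, and this point does not dispute it.

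**2. From tape to PWV.** PWV = D / t, so for an error e in D the error in PWV is PWV × e / D. For e = 1 cm:

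- 10 m/s and 50 cm: 10/50 = 0.20 m/s
- lowest, 8 m/s and 60 cm: 8/60 = 0.13 m/s
- highest, 12 m/s and 45 cm: 12/45 = 0.27 m/s

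One centimetre is thus 13% to 27% of the target. Producing a full 1 m/s would take 3.75 cm (45/12) to 7.5 cm (60/8).

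**3. Differential bias.** Suppose there is no true effect, 40 per group, SD 1.5, and a false between-arm shift b. The noncentrality is b / (1.5 × √(2/40)) and the critical value on 78 df is 1.991.

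| b (m/s) | Path error at 10 m/s, 50 cm | Noncentrality | Two-sided type I error |
|---|---|---|---|
| 0.1 | 0.5 cm | 0.30 | 6.0% |
| 0.2 | 1.0 cm | 0.60 | 9.1% |
| 0.3 | 1.5 cm | 0.89 | 14.3% |
| 0.5 | 2.5 cm | 1.49 | 31.3% |

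**4. Random tape noise.** Take 10 m/s and 50 cm, with fresh taping at each of two visits.

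- Tape SD 1 cm on the path: the noise in a two-visit change is 0.20 × √2 = 0.28 m/s. Variances add. If 1.5 is the SD of change without tape noise, it becomes √(1.5² + 0.28²) = 1.53, and power at 40 per group falls from 83.8% to 82.5%.
- Tape SD 1 cm on each of two distances whose difference is the path: the noise in one PWV value is 0.28 and in a change 0.40. Adding it gives SD 1.55 and power 81.2%. If 1.5 already contains it, removing it gives SD 1.45 and power 86.3%.
- Tape SD 2 cm on each distance: SD 1.70 and power 73.8% if added; SD 1.27 and power 93.6% if removed.

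Up to about 1 cm, noise is therefore worth one to three points of power. Only the largest assumed value makes it matter.

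**5. What reuse of the distance achieves.** With D fixed, the change in PWV depends only on transit times, apart from a common scale factor. A 1 cm error in a 50 cm path then alters a true change of 1 m/s by 1/50, or 0.02 m/s, instead of shifting one visit by 0.20 m/s. If the arms are instead compared on week-24 values, reuse removes no tape variance. What protects that comparison from bias is taping before the envelope is opened, so both parts of the fix are needed.

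**The case against.** Several objections are fair.

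- *Repeated taping is inferred.* Section 3.4 describes the procedure once and never says that it is repeated. A reader might take re-taping at every visit as stated. It is a sound inference for the three pulse wave visits, because taping is written as a step of the measurement, but it remains an inference. The same caution applies to visit 1a: a list of visit purposes need not be a sequence, though nothing else in the protocol puts the measurement first.
- *Re-taping may be legitimate.* The marks go where the pulse is strongest, and that place may move. An old distance paired with a new site would itself be wrong. This stands against reusing the distance alone; recording the sites and returning to them meets it.
- *The visual check.* A reader might infer that judging curves by eye feeds bias straight into PWV. The text does not support that: the criterion is written for the peripheral pulse wave, the recording that yields AIx, while PWV is a second set, and it stands beside numeric limits. Dropping it could weaken quality control, since the quality index rests on pulse height and repeatability, and a distorted but tall and repeatable curve could pass.
- *The single observer.* A reader might see this as the flaw. One observer removes between-observer variation; the weakness is the absence of masking.
- *Safeguards partly exist.* Medication is taken after the examination, and at visits 5a and 8a the measurement is listed ahead of drug handling. Neither prevents the observer from knowing the arm, and neither concerns the tape.

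**Conclusion.** The point holds in a limited form. The trial is open-label in effect, although the protocol does not use the term. Its primary endpoint depends on a hand-taped distance that no stated limit checks, and as written that distance can be taken with the arm known at baseline and at follow-up.

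The documents do not show that bias occurs, nor how large it would be. The 9-14% type I error is conditional on a bias of 0.2-0.3 m/s, SD 1.5 and 40 per group; the corresponding 1 to 1.5 cm of path assumes 10 m/s and 50 cm. A reader might also infer that tape noise undermines the sample size. It does not: the stated n reproduces, and noise of about 1 cm costs one to three points of power.

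The change is worth making because the route leads into the primary endpoint, the existing safeguards leave it open, and closing it needs only procedural wording.

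**What to change.** In sections 3.4 and 3.13, state that:

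1. At visit 1a, marking, taping and both sets of recordings are complete before the envelope is opened.
2. The sites are recorded relative to the suprasternal notch, and the same sites and baseline distances are used at visits 5a and 8a. A departure is allowed only as a documented exception.
3. At visits 5a and 8a the pulse wave measurement comes first, and the recording form shows neither the allocation nor earlier PWV values.
4. The visual check stays alongside the numeric limits, and each rejected recording is logged with its reason.

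The cost is wording and a slightly longer form; no extra staff or visits are needed. Two limits remain. A real change in body shape or in the usable pulse site would go unnoticed unless it is recorded as an exception. The observer may also still learn the arm from the patient, so this closes the taping route without masking the assessment as a whole.

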### 3.3 Endpoints

Primary endpoint is the difference in PWV measured by the tonometer (Millar, Houston, Texas, USA) and using the SphygmoCor® hard- and software.

Secondary endpoints are pulse wave morphology, evaluated by the AIx, BP, subendocardial viability ration (SEVR), heart rate, time to reflection (TR), ejection duration (ED), pulse pressure (PP), kidney function (estimated glomerular filtration rate (eGFR)), p-creatinine, AASI and albuminuria.

P-potassium and p-creatinine are used for safety monitoring.

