### 3.6 Study Population

Potential study participants are patients with CKD stages 3-4 (50), who at the time of recruitment are attending the outpatient clinics at the Departments of Nephrology at either Herlev Hospital or Rigshospitalet. Sponsor-investigator will be recruiting at both sites and all participants will be seen only at Herlev Hospital during the study period. Contact with potential participants will be made during a normal visit to the clinic or during admission to the ward.

Patients who fulfil inclusion criteria will be offered participation in the study. There is no financial compensation made in case of participation. Study medication is given free of charge.

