### 3.8 Exclusion criteria

Patients are ineligible for participation in the study if one of the following conditions is present:

- p-potassium is > 5.0 mM
- allergy to contents
- treated with spironolactone
- treated with potent inhibitors of CYP3A4 (see SPC for details)
- treated with lithium, ciclosporin, tacrolimus, prednisolone, or other immunosuppressing drug
- inborn errors of metabolism (see SPC for details)
- pregnancy or lactation
- fertile woman, not using safe contraception devices
- dementia or other psychiatric disorder, making understanding of the study conditions impossible
- other severe, chronic illness besides CKD, including liver insufficiency, according to investigators’ judgement
- vascular surgery including stenting or graftimplantation on a. brachialis, aorta or the carotid arteries
- systolic BP > 200 mmHg
- immeasurable pulse amplitude

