### 3.13 Practical performance of study

Patients who fulfil the inclusion criteria and who are interested in participating in the study are informed about the study. The written information is handed out and will be thoroughly explained. A form of written informed consent is to be signed by the patient and the informant/investigator. If consent is given, dates for the study days will be given.

Demographic data will be registered.

Randomization: When inclusion criteria are met including the performance of a screening for PW measurements and the run-in period has been completed, patients are randomized to the active treatment arm with eplerenone or the control arm for 24 weeks.

Planning:

A deviation of ± 1 week from the initially planned date for visits is permitted. Collection of 24 hour urine is allowed for at time deviation of ± 3 days with respect to blood sampling. Participants’ visits are planned to be identical in both groups.

Visits are planned as shown below:

| ***Visit number*** | ***Time with reference to inclusion for the individual patient*** | ***Purpose of visit*** | ***Estimated time used for the visit*** |
| --- | --- | --- | --- |
|  | Screening | signing of written informed consent, PW measurement test, ECG, blood sampling, demographic data noted | 1-1½ hours |
| 1a | Week 1 | randomization, PW measurement, AMBP, blood sampling, 24 h urine, study medication handed out | 1 hour |
| 1b | Week 1 | return of AMBP device | 10 minutes |
| 2 | Week 2 | blood sampling, BP, increase in study medication | 30 minutes |
| 3 | Week 4 | blood sampling, BP, study medication handed out | 30 minutes |
| 4 | Week 8 | blood sampling, BP, study medication handed out | 30 minutes |
| 5a | Week 12 | PW measurement, AMBP, blood sampling, 24 h urine, study medication handed out | 1 hour |
| 5b | Week 12 | return of AMBP device | 10 minutes |
| 6 | Week 16 | blood sampling, BP, study medication handed out | 30 minutes |
| 7 | Week 20 | blood sampling, BP, study medication handed out | 30 minutes |
| 8a | Week 24 | PW measurement, AMBP, blood sampling, 24 h urine, study medication and packages returned | 1-1½ hours |
| 8b | Week 24 | return of AMBP device | 10 minutes |

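### The increase from 25 to 50 mg eplerenone at visit 2 does not depend on the potassium and creatinine sampled at that visit

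*Protocol*

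**What the plan says.** Protocol section 3.4 (study medication) gives a starting dose of 25 mg once daily and continues: "The dose will be increased to 50 mg eplerenone in once daily dosing after 1 week". The visit table in section 3.13 gives the purpose of visit 2, in week 2, as "blood sampling, BP, increase in study medication". Neither place attaches a condition.

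The laboratory table in section 3.11 includes potassium and creatinine in the visit 2 bloods, and section 3.3 gives their role: "P-potassium and p-creatinine are used for safety monitoring".

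The one rule on adjusting the dose is in section 3.2: "If study participants fail to tolerate the full dose of eplerenone 50 mg once daily, dose will be reduced to 25 mg once daily".

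On who is treated, section 3.6 says "Potential study participants are patients with CKD stages 3-4", and section 3.7 sets eGFR from 15 to below 60. Section 3.2 adds: "All patients are to continue on their normal medication including blockers of RAS, which most of these patients receive before enrolment". Section 3.8 excludes a patient if "p-potassium is > 5.0 mM". In section 3.9 the potassium criterion for withdrawal is hyperkalaemia that is severe and cannot be treated, without a number. The creatinine criterion is a lasting rise of more than 30% over baseline at the first control visit. Both are things for which the investigators may withdraw a patient; neither is mandatory.

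**The concern.** The week 2 sample is the only scheduled on-treatment look at potassium and creatinine before the dose is doubled. A reader expects its result to decide whether the dose goes up. The protocol places the sample and the increase at the same visit and does not connect them: it sets no value at which the increase is held, and it does not say that the result must be seen first.

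The population makes this matter. Kidney function is reduced by design, most patients stay on drugs that block the renin-angiotensin system, and the section on ethical considerations lists hyperkalaemia and reduced kidney function among the common side effects of the drug. That section answers the hyperkalaemia risk by pointing to close monitoring. Monitoring protects a patient at this step only if the result can change the step.

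**Working it through.** The protocol states no figure on this point, so the check is a comparison of its rules plus simple counts from the schedule. The sample-size calculation does not enter.

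**Counts from sections 3.4, 3.8, 3.9, 3.11 and 3.13**

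- Size of the step: 50 / 25 = 2, a doubling.
- Planned time on 25 mg: week 1 to week 2 = 7 days.
- Scheduled samplings after the first dose: visits 2, 3, 4, 5a, 6, 7 and 8a = 7. Those before or at the increase: 1 (visit 2).
- Numeric potassium limits: 1 at entry (5.0 mM), 0 on treatment.
- Next scheduled sample after the increase: (4 − 2) × 7 = 14 days. Section 3.13 says "A deviation of ± 1 week from the initially planned date for visits is permitted", so with visit 2 on time and visit 3 one week late it is 14 + 7 = 21 days.

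These counts describe the schedule and do not measure harm. The 14 to 21 days to the next sample would be the same for every escalated patient under a conditional rule, so that interval is not evidence for the point.

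**What each rule does for a patient at visit 2, after one week on 25 mg**

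- *Potassium above 5.0 mM, but treatable or not severe.* The entry limit no longer applies. The withdrawal criterion is not met. The rule in section 3.2 concerns patients who have failed 50 mg, and this patient has not yet had it. What remains is the instruction to increase.
- *Creatinine more than 30% above baseline.* The investigators may withdraw the patient if the rise persists. No rule provides for holding at 25 mg while that is established. If they do not withdraw the patient, the increase stands.
- *Creatinine up by 30% or less, potassium at most 5.0 mM, no side effects.* The increase goes ahead, as it would under a conditional rule.
- *Side effects on 25 mg that do not lead to withdrawal.* The reduction rule again presupposes 50 mg, so the increase stands.

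**Whether another place supplies the condition**

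- The product characteristics are cited in section 3.4 as the reference for judging side effects, and in section 3.8 for details of two exclusion criteria. Neither citation makes them a titration rule.
- The section on adverse events recognises that a laboratory result may lead to a change in study medication. It does so only when defining which abnormal results need not be recorded as events, and it does not mention the visit 2 increase.

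No rule in the protocol closes the first case.

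**The case against.** The best reply is that silence is not an instruction to ignore the result. Visit 2 lists blood sampling and blood pressure ahead of the increase, potassium and creatinine are named as safety measures, the frequent visits are justified by timely detection of hyperkalaemia, and the adverse-event section takes it as normal that investigators act on laboratory values. No blinding is described that would hide potassium or allocation. Potassium supplements are stopped beforehand, spironolactone and potent CYP3A4 inhibitors are excluded, and the group reports good experience with eplerenone in such patients.

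Much of this stands. A reader might infer that the protocol tells investigators to disregard a high potassium, or that patients would in practice be escalated regardless. The document supports neither: experienced nephrologists would probably hold the dose. But they would then depart from a dosing sentence written without exception, and each would choose a limit ad hoc. The safeguards lower the risk without making the increase conditional.

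Two further inferences fail. The reduction rule in section 3.2 and the withdrawal of patients with unacceptable side effects may look contradictory, but they read naturally as reduce first, then withdraw if that does not help. The creatinine criterion may look ambiguous about its baseline, but the mention of the first control visit most naturally says when the rise is judged.

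**Conclusion.** The point holds as a defect in a stated dosing rule. The protocol doubles the dose at visit 2 without a condition, its one dose rule acts only after the higher dose has failed, and no potassium limit applies on treatment. A patient whose potassium has passed the trial's own entry limit on 25 mg is, as written, taken to 50 mg. The gap is clearest for potassium; for creatinine there is a 30% criterion, but it offers optional withdrawal and no hold.

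The size is limited. How often this would occur cannot be derived, because the side-effect frequencies are not given by week. It is a matter of safety and dosing. A reader might infer that the power or the pulse wave velocity comparison is affected; nothing in the document supports that, and it is not claimed.

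The conclusion rests on taking the dosing text in sections 3.4 and 3.13 as the operative instruction. The change should be made, since the needed results are already collected.

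**What to change.** In sections 3.4 and 3.13, with a cross-reference in section 3.2, make the increase conditional. Suggested content:

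- Increase to 50 mg only after the visit 2 results have been reviewed and show potassium at most 5.0 mM and creatinine not more than 30% above the visit 1a value, with no unacceptable side effect. The 5.0 mM figure is the trial's own entry limit; the sponsor may set another with a reason.
- Otherwise stay on 25 mg, or stop if continuing is judged unsafe. Repeat the test no later than visit 3, and increase only if the same limits are then met.

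The withdrawal criteria can stay as they are.

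Cost: wording in three sections, with no added scheduled visits or patients, since visits 2 and 3 already include both tests. Samples go to the hospital's central laboratory and no turnaround time is given, so the increase may have to be confirmed by telephone once results are back. An occasional unscheduled repeat test may be needed. Some patients, in a number that the document does not allow to be estimated, will reach 50 mg later or not at all.
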